### The empirical base of DBT-PTSD

Following the usual process of evaluating a new treatment, as a first step, we carried out a non-controlled clinical pilot trial on residential DBT-PTSD treatment on 29 women who suffered from PTSD after CA and at least one other co-occurring diagnosis [65]. An effect size of Cohen's d = 1.22 on the Posttraumatic Diagnostic Scale (PDS; [66]) was found between baseline and the follow-up 6 weeks after the end of the 12-week programme. Effect sizes for secondary outcomes ranged from medium to large. The results suggested that DBT-PTSD is a very promising treatment for reducing severe PTSD after CA.

Next, we conducted a RCT in which women (*N* = 74) diagnosed with PTSD after CA plus at least one of the following additional diagnoses/symptoms: at least 4 DSM-IV criteria of BPD, current major depressive disorder, eating disorder, or alcohol and drug abuse were randomised to either the 12-week residential DBT-PTSD programme or a treatment-as-usual waiting list (TAU-WL) [67]. The two primary outcomes were scores on the Clinician-Administered PTSD Scale (CAPS; [68]) and on the PDS [66]. All measurements were done by blind raters. Only 6% of the DBT-PTSD group (2 out of 36) discontinued the treatment prematurely. Hierarchical linear models yielded statistically significant group*time effects, indicating a more pronounced improvement in the DBT-PTSD group compared to the TAU-WL, with large effect sizes. Between-group effect sizes were large for the CAPS (Hedges’s g = 1.57), PDS (g = 1.27), Global Assessment of Functioning (GAF, [69]; g = 1.31), and Beck Depression Inventory-II (BDI-II, [70]; g = 1.13). No patient in the DBT-PTSD group showed worsening of posttraumatic symptoms or exaggerated dysfunctional behaviour [67, 71]. Neither BPD symptom severity, the number of BPD criteria, nor self-harm behaviour had a significant influence on treatment outcome. Our findings provided clear evidence for the efficacy, high tolerability, and safety of the newly developed DBT-PTSD under residential conditions.

In preparation for the trial on hand, we have adapted the DBT-PTSD manual to outpatient conditions. DBT-PTSD now consists of a 1 year multi-component treatment providing up to 45 sessions à 50 min (37.5 h hours in total) of individual therapy (and telephone consultation as needed) plus up to 3 additional booster sessions during the following 3 months. These booster  sessions mainly focus on implementation of relevant treatment aspects in daily live. We have tested the manual in a pre-post pilot study that enrolled 20 patients with PTSD after CA plus at least 4 BPD criteria, and found similar results to those obtained under residential conditions (effect size CAPS: Cohen’s d = 1.5) [72].

Unlike current state-of-the-art treatments for PTSD, which typically consist of 12 to 16 sessions, we decided on a longer treatment duration and more treatment sessions as justified by the following:The included patients suffer not only from PTSD but also from severe emotional dysregulation and serious dysfunctional behavioural patterns including self-harm behaviour. Standard DBT programmes that do not focus on PTSD usually last at least 1 year [73–75];The successful residential programme consists of twice-weekly 45-min sessions of individual treatment (a total of 23 sessions over the 12 weeks) plus the following weekly group treatments: 90 min of skills training (11 sessions in total), 60 min of group intervention focusing on self-esteem (8 sessions in total), three 25 min mindfulness sessions (35 sessions in total), as well as 60 min of PTSD-specific psychoeducation (11 sessions in total) and three 90- min non-specific weekly group interventions (music therapy, art therapy).

In the trial on residential DBT-PTSD, we found an average reduction of PTSD symptoms as assessed by the CAPS from 88 at admission to 55 at discharge [67]. Despite this clinically significant reduction in the primary outcome, many of the patients needed further psychotherapy after discharge. Taken together, 45 sessions of outpatient treatment is a minimum, and is justified for scientific and ethical reasons. Furthermore, the German health care system in general covers the costs for up to 80 sessions of behaviour therapy. Designing a short-term therapy for this group of severely disturbed patients would be unrealistic and would not fit into the frame of the German health care system. To facilitate transfer into routine conditions, we further decided to provide all psychotherapeutic sessions in an individual format. This allows to disseminating these treatments to rural regions which have little access to psychotherapeutic supply.

### Cognitive processing therapy (CPT)

We chose CPT as an adequate active control condition. In close cooperation with [name] (Duke University, Durham, USA), the developer of this treatment, we have adapted the established protocol for CPT (cognitive only version) to a 1 year  outpatient individual therapy programme comprising up to 45 sessions plus up to 3 additional booster sessions during the following 3 months. Thus, dosage and frequency of both treatments are equal.

The protocol has been translated and has been approved by [name], who serves as a cooperation partner and supervisor. We have further translated and adapted the rating for therapeutic adherence for CPT on the basis of the ones used by Resick et al. [45, 76].

To ensure treatment fidelity therapists receive 1.5 h per week team consultation with local supervisors. In addition, the local supervisors have monthly case-consultations with the treatment developer [name].

Individual sessions follow a session-by-session protocol. In addition to building an effective therapeutic alliance, the first 4 sessions aim to obtain a detailed case history, patient’s specific problem behaviour, and emergency plans. The next 12 sessions contain the original 12 CPT core sessions, starting with psychoeducation about PTSD and the treatment rationale. After the patient has written an impact statement as to why the trauma has happened and how it affected her beliefs, cognitive restructuring is applied with regard to guilt and denial. Then, worksheets are introduced step by step which are intended to support the patient in identifying and changing other dysfunctional trauma-related beliefs (the so-called stuck-points) regarding safety, trust, control and power, self-esteem, and intimacy. From session 17 onwards, the content of the sessions is derived from the patient’s individual stuck point log. After working on the index trauma, and writing a second impact statement, other traumatic incidents can be the treatment focus. Towards the end of the treatment, other goals of the patient (positive activities, social relationships, vocational training or work issues) can be addressed using the already established cognitive techniques.

## Design

### Work plan

The three goals of this collaborative research group are:To evaluate the efficacy and effectiveness of a newly developed outpatient psychotherapy programme tailored specifically for patients suffering from cPTSD after childhood physical and sexual abuse (Main project)To assess the role of treatment integrity (therapeutic adherence and competence) for treatment outcome of DBT-PTSD and CPT (Adjunct project I)To study the impact of successful treatments on the neurophysiological underpinnings of dissociation and intrusions (Adjunct project II)

### Main project

#### Hypotheses

Improvement of PTSD symptoms will be superior in DBT-PTSD as compared to CPT.The superiority of DBT-PTSD over CPT is related to the severity of BPD symptoms at baseline.

#### Additional analyses

The collected data will enable us to additionally test potential moderator variables for both, general and differentiated treatment response: a) Client variables including severity of CA, age at the onset and duration of CA, pre-treatment severity of PTSD and dissociation, co-occurring depressive disorder, current age, and educational level; b) Therapist variables including length of experience and gender.

#### Health care costs

As cPTSD is related to very high health care costs, we will also address this aspect. Direct and indirect costs will be compared across treatments and will be further compared with costs related to other epidemiologically relevant mental disorders. The reference time frames will be 1 year before the start of the treatments, at the end of treatments, and at 1 year follow-up. State of the art methodology will be applied (e.g., [77–80]), including a questionnaire and a structured interview to assess health care costs.

#### Inclusion criteria

We include female subjects between the ages of 18 and 65 who have a primary diagnosis of DSM-5–defined PTSD related to childhood sexual abuse or childhood physical violence before the age of 18. In addition, the patients have to meet at least 3 DSM-5 criteria for BPD (including criterion 6, affective instability). Furthermore, the patients have to be available for 1 year of outpatient treatment with no scheduled absence of more than 4 weeks, have to understand the implications related to the participation in a clinical trial, and have to give their written informed consent prior to randomisation.

#### Exclusion criteria

Exclusion Criteria are a lifetime diagnosis of schizophrenia or bipolar I disorder, mental retardation, severe psychopathology requiring immediate treatment in a different setting (such as acute alcohol withdrawal syndrome, or BMI < 16.5), current substance dependence without abstinence within the last 2 month, life-threatening suicide attempts as assessed by the Severe Behaviour Dyscontrol Interview (SBDI, [81]) within the last 2 months, medical conditions contradicting exposure protocol (e.g., severe cardiovascular disorder), pregnancy, currently severe instable life situations (e.g., homelessness, or ongoing victimisation by the perpetrator), or treatment with CPT or DBT-PTSD within the last year. Patients with ongoing self-harm or high-risk behaviours are accepted in the study.

#### Randomisation and blinding procedures

Before the start of the study, patients who meet the eligibility criteria are randomised in 1:1 ratio to either DBT-PTSD or CPT. Concealed assignment to the treatment groups is assured by using an external, web-based randomisation service (http://randomizer.at, University of Graz, Austria). All persons involved in the diagnostics and ratings are blinded with respect to the group assignment.

#### Crisis management

Both interventions develop safety plans at treatment start, and employ active crisis intervention when needed. Similar to standards of care, therapists provide on-call after-hours service via area crisis services. Patients in both groups have access to emergency services when viewed as necessary by therapists in the respective conditions. Inpatient services are readily available across conditions and across sites.

#### Hospitalisation policy

Because of the nature of the population, some patients may require treatment in a psychiatric hospital, either at their own request or due to the concerns of care providers (usually due to high acute suicide risk). No outpatient therapist will serve in a responsible position for any patient (e.g., attending) during inpatient treatment. Study treatment will be terminated when patients are hospitalised for more than 2 weeks.

#### Psychotropic medication protocol

There is no established pharmacological treatment protocol for PTSD after CA. On the other hand, tapering patients off medication would restrict recruitment to a small number of patients with less severe pathology and would be at the cost of external validity. We decided to track week-by-week medications and medication changes in order to document any difference in medication management across conditions. The purpose of the study is not to evaluate the efficacy of a combination of psychotherapy and a psychopharmacologic algorithm, but rather to evaluate psychotherapy interventions under conditions similar to those encountered in the community.

#### Dropout policy

Besides patients prematurely terminating therapy, any patient who misses 6 consecutively scheduled weeks of individual therapy or stays longer than 2 weeks in a psychiatric hospital will be considered a drop-out from treatment. This rule was instituted because it can be very difficult to know exactly when an emotionally dysregulated patient has actually dropped out of therapy. Often, patients miss sessions because of mood swings, discouragement, or interfering day-to-day hassles, but they do not mean to drop out of treatment and they often change their minds within a short period of time. This drop-out rule will be explained to patients during the first session of individual therapy. It is conceivable that some patients achieve the treatment goals (full symptomatic remission) and want to terminate the treatment prior to 1 year of treatment. The study protocol foresees the possibility of an early remission: No longer fulfilling the diagnostic criteria of PTSD, as assessed by the Clinician-Administered PTSD Scale for DSM-5 (CAPS-5; [82, 83]), as well as the approval by the patient, the therapist and the supervisor. Patients who have achieved an early remission are not considered having dropped out of the study.

#### Protocols to prevent cross-contamination between DBT-PTSD and CPT conditions

To reduce contamination, CPT and DBT-PTSD are not provided by the same therapists. Treatment fidelity will be supported by regular team consultation, including video-based real-time supervision in both treatments. Protocol violations will be reported to the therapists immediately. Therapeutic training and experience of the therapists will be balanced across treatment groups.

#### Therapists, training, and treatment adherence

At each of the three sites, therapists have been either trained in DBT-PTSD or in CPT. DBT-PTSD therapists at each site have been trained by the treatment developers, CPT therapists at each site have been trained by [name]. Therapists were asked to videotape every session. A randomly selected 2 of the 45 sessions of each therapy are being evaluated with regard to treatment integrity. DBT-PTSD treatment adherence is evaluated by using the DBT-PTSD Adherence Rating Scale, which generates a global rating of DBT adherence as well as sub-scale strategy ratings for various DBT-PTSD strategy domains. CPT treatment adherence is evaluated using the CPT Adherence Ratings Scale, which is based on the adapted CPT treatment manual and orientated on the original CPT Therapists’ Adherence Protocol – Revised [84] and has been adapted to the present CPT manual by [name]’s workgroup [76].

#### Assessments

Assessments will be conducted by blind raters at intake and at months 3, 6, 9, 12, 15 (end of the treatment phase) and at 1 year follow up. In addition to these assessments, in DBT-PTSD weekly measurements will be completed in the form of a daily diary card, rating of suicidal ideation, non-suicidal self-injury, therapist notes, and pre- and post-session ratings for each individual session.

#### Screening measures

Structured Clinical Interview for DSM-IV Axis I Disorders (SCID-I; [85]); CAPS-5 [82, 83]; International Personality Disorder Examination – Borderline section (IPDE; [86]); SBDI [81]; Childhood Trauma Questionnaire (CTQ; [87]), Maltreatment and Abuse Chronology of Exposure Scale (MACE; [88]), Mehrfachwahl-Wortschatz-Intelligenztest (MWT; [89]).

#### Primary and secondary endpoints

The CAPS-5 [82, 83] will be used as the primary endpoint for testing hypotheses 1 and 2. In the first place testing will be based on the dimensional CAPS-scores assessed in the intent-to-treat sample. Secondary endpoints will include the Posttraumatic Stress Disorder Checklist for DSM-5 (PCL-5; [90]) to assess self-rated symptomatology of PTSD, the Dissociation Tension Scale (DSS-7, [91]), the short version of the Borderline Symptom List (BSL-23; [92]), the behavioural items of the Borderline Symptom List [93] including suicide attempts and non-suicidal self-injury, the BDI-II [70], and the GAF [69].

#### Power analyses

The sample size was determined from a formal power analysis. The study was designed to have sufficient statistical power (1-β ≥ 0.80) to detect a supposed medium-size superiority of DBT-PTSD over CPT for the time*treatment interaction. A no more than medium between-group effect-size (d = 0.5, which corresponds to an effect-size f(V) of 0.354 for the time*treatment contrast for DBT-PTSD vs. CPT within a repeated measures design) was assumed since CPT was supposed to be substantially more efficacious than the TAU-WL condition to which DBT-PTSD has been previously compared. Under these assumptions, data from 70 participants per group are required to achieve sufficient statistical power (1-β ≥ 0.80) for Hypothesis 1. For Hypothesis 2 (“the superiority of DBT-PTSD is related to the severity of BPD-symptoms at baseline”) the power analysis indicated that a sample-size of at least 90 per group is needed to achieve sufficient statistical power to detect a clinically meaningful incremental R^2^ of at least 0.1 within a regression model. Accordingly, the recruitment target was set at a minimum of 180 participants (90 per group) to be randomised. In order to recruit and treat a minimum of 180 patients within 2 years, the study is conducted at three large German centres: the Central Institute of Mental Health in Mannheim, the Institute of Psychology, Goethe University in Frankfurt, and the Institute of Psychology, Humboldt University in Berlin.

#### Statistical analysis

The CAPS-5 and the assessments pertaining to the secondary hypotheses are obtained at baseline (=T1); at month 3 (=T2); month 6 (=T3); month 9 (=T4); month 12 (=T5, end of high frequency phase); and month 15 (=T6, end low frequency phase = post assessment). Mixed linear models including these assessment points will be used as the primary analytic strategy to analyse and compare the changes in the two groups. Parameters will be estimated using restricted maximum likelihood estimates (REML) and without imposing predefined assumptions such as compound symmetry on the covariance matrix. Analyses are based on the intent-to-treat sample of patients who were randomised and fulfilled all inclusion criteria. To provide a more complete picture these primary analyses are complemented by analyses comprising those participants who completed the study according to protocol (ATP). To allow for a more comprehensive evaluation of the data, the results from the mixed linear models are supplemented by clinically meaningful indices including remission rates, response rates and effect sizes.

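### As usually fitted, the primary mixed model with baseline CAPS-5 as a response is unbiased but less precise than one that holds the baseline means equal across arms

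*Protocol article*

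**What the plan says.** The Statistical analysis section of the main project lists the CAPS-5 visits. Scores "are obtained at baseline (=T1); at month 3 (=T2); month 6 (=T3", then at months 9, 12 and 15 (T4 to T6). It goes on: "Mixed linear models including these assessment points will be used as the primary analytic strategy to analyse and compare the changes in the two groups". Estimation is by REML, "without imposing predefined assumptions such as compound symmetry on the covariance matrix", which I read as an unstructured covariance.

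The Power analyses section names the effect for Hypothesis 1. The study is sized "to detect a supposed medium-size superiority of DBT-PTSD over CPT for the time*treatment interaction", with "d = 0.5, which corresponds to an effect-size f(V) of 0.354 for the time*treatment contrast", and "data from 70 participants per group are required to achieve sufficient statistical power (1-β ≥ 0.80) for Hypothesis 1". Hypothesis 2 raises the recruitment target to 90 per group.

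The Abstract gives the primary outcome as change on the CAPS-5. No baseline CAPS-5 covariate is named for the main analysis. Pre-treatment CAPS is controlled for explicitly in Adjunct project I. In the main project, pre-treatment PTSD severity appears only among the possible moderators under Additional analyses.

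**The concern.** T1 is one of the modelled time points and the test is time*treatment, so baseline sits in the response vector. A model of this kind is usually fitted with a separate T1 mean for each arm. In a randomised trial the true T1 means are equal, so the extra parameter estimates a difference known to be zero. Its sampling error is then subtracted from the treatment effect at every later visit.

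What is at stake is precision on the primary hypothesis. The interval around the arm difference would be wider, and power lower, than the same data allow. The authors specify baseline control in Adjunct project I and do not mention it here, which makes free T1 means the natural reading of the main analysis.

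**Working it through.** **Inputs from the article.** T1 to T6 as responses; unstructured covariance; time*treatment test; d = 0.5; 70 per group for Hypothesis 1; 90 per group planned; 1:1 allocation.

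**Inputs not given, so assumed.** Two-sided alpha 0.05 for the main project; T1-T6 correlation ρ from 0.3 to 0.8; SDs s0 at T1 and s1 at T6, with s1/s0 from 1.0 to 1.5; d scaled on the raw T6 SD.

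**1. The article's own figure.** A two-group comparison with d = 0.5 needs 2(1.960 + 0.842)²/0.25 = 62.8, so 63 per arm (64 by the t distribution). With 70 per arm, power is 0.841 (0.836 by t). The stated condition of at least 0.80 is met, but 70 is not the minimum by this route. Reading f(V) = 0.354 into a repeated-measures F test gives 33 per arm with 1 df or 55 with 5 df. That mismatch is a separate matter and does not affect this point.

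**2. Variance per patient, complete data.**
- Free T1 means (difference in change): s0² + s1² − 2ρ·s0·s1
- Common T1 mean, or T1 as covariate: s1²(1 − ρ²)
- First minus second: (s0 − ρ·s1)²

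The difference is a square, so adjustment never loses in large samples. It gains nothing where ρ·s1 = s0. With equal SDs the ratio of adjusted to unadjusted variance is (1 − ρ²)/[2(1 − ρ)] = (1 + ρ)/2.

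**3. Check on the six-visit model itself.** With ρ = 0.5, equal SDs and 70 per arm, generalised least squares with free T1 means gives a variance of 0.0286 for the T6−T1 contrast, which is the change-score value 2 × 1.00/70. With T1 still a response but a common T1 mean, it gives 0.0214, which is the ANCOVA value 2 × 0.75/70. The ratio is 0.75. With 25% monotone dropout (5% lost after each visit, correlation 0.5 between all visits), the variances are 0.0346 and 0.0275, ratio 0.794.

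**4. Power at the planned 90 per arm**, by Φ(0.5/√(2v/90) − 1.96), with v in units of s1²:

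| ρ | s1/s0 | v unadjusted | v adjusted | ratio | power unadjusted | power adjusted |
|---|---|---|---|---|---|---|
| 0.3 | 1.0 | 1.40 | 0.91 | 0.65 | 0.809 | 0.940 |
| 0.5 | 1.0 | 1.00 | 0.75 | 0.75 | 0.918 | 0.972 |
| 0.7 | 1.0 | 0.60 | 0.51 | 0.85 | 0.991 | 0.997 |
| 0.5 | 1.25 | 0.84 | 0.75 | 0.893 | 0.955 | 0.972 |
| 0.5 | 1.5 | 0.778 | 0.75 | 0.964 | 0.967 | 0.972 |
| 0.8 | 1.25 | 0.36 | 0.36 | 1.00 | about 1 | about 1 |

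Example for the second row: 0.5/√(2 × 1.00/90) = 3.354, less 1.96 is 1.394, power 0.918. Adjusted: 0.5/√(2 × 0.75/90) = 3.873, less 1.96 is 1.913, power 0.972.

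**The case against.** The strongest reply is that the article does not say that the T1 means are free. A constrained model also has T1 as a response, REML and an unstructured covariance, so it fits the published wording, and the detail may sit in a document not shown. This stands in part. A reader might infer that listing T1 as a response by itself forces an unadjusted comparison; step 3 shows that it does not. What remains is that free T1 means are the conventional form of a time*treatment test, and that the article is explicit about baseline control where it intends it.

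Second, nothing here is invalid. A reader might take chance baseline imbalance as a source of bias. It is not: under randomisation the difference in change is unbiased with a valid type I error rate, and the imbalance is the same variance counted once. This stands in full.

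Third, the size is uncertain. The simple ratio (1 + ρ)/2 needs equal SDs. The identity with a change score is exact only with complete data, and dropout is foreseen. Quoting power at 70 per arm and low correlation (0.705 against 0.873 at ρ = 0.3) makes the loss look large, but 90 per arm are planned. The article also does not say that d is on the raw SD. If d is on the SD of change, unadjusted power is about 0.84 at 70 and 0.92 at 90, whatever ρ is. All of this stands.

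A reader might also argue that selecting patients on a PTSD diagnosis lowers ρ and so makes the loss largest. The documents do not support that: restricting the baseline range also lowers s0, which works the other way.

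**Conclusion.** The point holds as one of efficiency, on the conventional but unstated reading that the T1 means are free. On that reading the planned contrast is unbiased and, in large samples, never more precise than the constrained version. With equal SDs, adjustment leaves 65%, 75% or 85% of the variance at ρ = 0.3, 0.5 or 0.7, and about 79% at ρ = 0.5 with 25% monotone dropout. If the SD grows after baseline by a factor of 1.25 to 1.5, the figure at ρ = 0.5 is 89% to 96%, and the gain is nil where ρ·s1 = s0. My central illustration is a rise in power from about 0.92 to 0.97 at 90 per arm. It rests on ρ = 0.5, equal SDs, complete data, d = 0.5 on the raw SD and two-sided 0.05; of these the article gives only d = 0.5, without its scale. Confidence in the direction is high, and in the size low. The change is worth making because it costs almost nothing and bears on the primary hypothesis.

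**What to change.** Add one sentence to the primary analysis: CAPS-5 at T1 to T6 are the responses, with REML and an unstructured covariance as now; the T1 mean is constrained to be equal in the two arms; and the arm effects at the visits after T1 are tested. Because the T1 means are equal by design, these effects still estimate the difference in change, so the stated primary outcome is kept. Patients with only a T1 assessment stay in the intent-to-treat model, whereas modelling T2 to T6 with T1 as a covariate would leave them out. If this model is already intended, the sentence simply says so.

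The cost is one line of specification and no new data. It should be settled before unblinding, so that the choice cannot follow the baseline imbalance that is observed.

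### The only comparison named for secondary assessments, a linear mixed model of change, does not suit suicide attempts or self-injury counts and can leave an excess in one arm unseen

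*Protocol article*

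**What the plan says.** All references are to the main project of the protocol article.

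- **Primary and secondary endpoints** lists, among the secondary endpoints, "the behavioural items of the Borderline Symptom List [93] including suicide attempts and non-suicidal self-injury".
- **Statistical analysis** opens with the measurements it covers: "The CAPS-5 and the assessments pertaining to the secondary hypotheses are obtained at baseline (=T1); at month 3 (=T2") and onwards to month 15 (T6). It then gives the method: "Mixed linear models including these assessment points will be used as the primary analytic strategy to analyse and compare the changes in the two groups". Estimation is by REML, "without imposing predefined assumptions such as compound symmetry on the covariance matrix". The supplements it names are remission rates, response rates and effect sizes. None is a count of events or a proportion of patients with an event.
- **Power analyses** names the time-by-treatment interaction as the tested effect and sets the target at 90 per group.
- **Assessments** gives the schedule: "Assessments will be conducted by blind raters at intake and at months 3, 6, 9, 12, 15 (end of the treatment phase"), plus a 1-year follow-up. Weekly ratings that include self-injury are described for DBT-PTSD only.
- **Exclusion criteria** removes patients with "life-threatening suicide attempts as assessed by the Severe Behaviour Dyscontrol Interview (SBDI, [81]) within the last 2 months", but accepts patients whose self-harm is ongoing.

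**The concern.** A Gaussian model of mean change is natural for the CAPS-5, PCL-5 or BDI-II. Suicide attempts are different: at any visit most patients have none. The visit means then lie near zero, their variances depend on those means, and a visit without a single event has zero variance, so an unconstrained covariance matrix becomes singular. A test with one degree of freedom per post-baseline visit also spreads a few events over five comparisons.

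The reference point is awkward too. Because life-threatening attempts in the 2 months before entry are an exclusion, T1 is held down by selection for such attempts, and subtracting it adds noise or nothing.

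For self-injury the difficulty is not rarity, since ongoing self-harm is accepted, but skewed counts.

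At stake is the between-arm comparison of attempts and self-injury, in a trial that admits patients with ongoing self-harm and compares skills-assisted exposure with a purely cognitive treatment. Followed as written, the plan could report no difference in change, or fail to fit, when one arm had about three times as many patients with an attempt.

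**Working it through.** **Plan's own figure.** There is none to reproduce. The document gives no event rate, effect size or power for these items.

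**Inputs from the document.** n = 90 per arm, 1:1 allocation, five post-baseline visits (T2 to T6), unstructured covariance, time-by-treatment test.

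**Assumptions (not in the document).** Event risk per visit in each arm, constant over visits; within-patient correlation 0.10 (beta-binomial); complete data; no events at T1 in the main scenarios; two-sided 5% level.

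**Step 1: patients with any event.** With a + b = 1/0.10 − 1 = 9 and b = 9(1 − p), the risk of any event over five visits is 1 − ∏(b + i)/(9 + i), i = 0 to 4.

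- p = 0.02: b = 8.82, risk 0.080. p = 0.06: b = 8.46, risk 0.226. Expected patients: 90 × 0.080 = 7.2 vs 90 × 0.226 = 20.3.
- p = 0.01: risk 0.041. p = 0.03: risk 0.119. Expected patients: 3.7 vs 10.7.

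**Step 2: the named test.** With complete data, the unstructured time-by-treatment test is taken as Hotelling's T² on the five changes from T1: T² = (n/2) d′S⁻¹d, with F = T²(2n − 6)/[5(2n − 2)] = T² × 174/890 on 5 and 174 df. Here d is the vector of arm differences and S the pooled covariance. The alternative is Fisher's exact test on any event over T2 to T6.

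| Risk per visit | Time-by-treatment test | Fisher, any event | Singular covariance |
|---|---|---|---|
| 2% vs 6% | 0.44 | 0.73 | rare |
| 1% vs 3% | 0.11 | 0.39 | 13% |
| 0.5% vs 1.5% | 0.01 | 0.15 | 60% |

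Singular runs count as no rejection. With no true difference at 2%, the time-by-treatment test rejects in about 1.2% to 1.4% of trials, so it is conservative. The problem is lost power and fit, not false positives.

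**Step 3: singularity by hand.** Treating visits as independent, the chance that one visit has no event in either arm at 1% vs 3% is 0.99⁹⁰ × 0.97⁹⁰ = 0.405 × 0.0645 = 0.026. Over five visits, 1 − (1 − 0.026)⁵ = 0.12. At 0.5% vs 1.5%: 0.637 × 0.257 = 0.163, and 1 − (1 − 0.163)⁵ = 0.59. Both agree with the simulation.

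**Step 4: a different model.** Poisson events in five 3-month windows, every event captured, and a T1 level of 5% to 10%:

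| 15-month incidence | Time-by-treatment test | Fisher, any event |
|---|---|---|
| 5% vs 15% | 0.07 to 0.19 | 0.54 to 0.56 |
| 5% vs 20% | 0.07 to 0.40 | 0.82 to 0.87 |

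The lower linear-model values are for a constant hazard, the higher for an excess in early to mid treatment. The normal-approximation power for two proportions at 90 per arm is 0.61 for 5% vs 15%: (0.10√90 − 1.96√(2 × 0.10 × 0.90))/√(0.0475 + 0.1275) = 0.28, and Φ(0.28) = 0.61. For 5% vs 20% it is 0.87. The gain therefore does not depend on one simulation model, nor on choosing a liberal comparator.

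**The case against.** **The text is general and condensed.** The Statistical analysis section does not name the behavioural items, and the main-project hypotheses concern PTSD symptoms only. A SAP, which is not shown, may treat these items separately. This stands as a caution, and the lack of an adverse-event table is no finding. But the items are listed secondary endpoints, and the section's wording on secondary assessments most naturally reaches them. It names one comparative method and no event-based supplement, so the point is about a method that is fixed, not about a gap.

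**A better linear contrast exists.** The average difference over T2 to T6 recovers most of the power: about 0.77 at 2% vs 6%. That holds only with nobody reporting an event at T1. With an assumed independent 5% rate at T1 it falls to 0.21, and it is not the time-by-treatment test that the power section names.

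**Stronger readings that a reader might infer, and that the document does not support:**

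- *The model compares only T1 with T6.* It uses all six assessments. An attempt at month 4 that is reported at T3 is in the model.
- *Most events go unseen.* This depends on the recall window of the items, which is not given. With full-interval recall none is lost by timing, and an any-event analysis of the same visits would miss whatever they miss.
- *This is the main known harm.* The document does not say so, and it reports no exaggerated dysfunctional behaviour in the DBT-PTSD group of the earlier residential trial.
- *Self-injury is rare and starts from a floor.* Ongoing self-harm is accepted. Rarity and the floor apply to attempts.
- *Patients hospitalised for suicide risk vanish from the analysis.* The Dropout policy says a patient who "stays longer than 2 weeks in a psychiatric hospital will be considered a drop-out from treatment". That is drop-out from treatment, not from assessment. The Hospitalisation policy gives a usual reason for admissions, "due to the concerns of care providers (usually due to high acute suicide risk"), but nothing says that the reason is recorded for each patient.

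**Conclusion.** The concern holds in limited form. On its natural reading, the protocol applies a Gaussian model of change with unstructured covariance to an endpoint made of sparse attempts and skewed self-injury counts. For attempts, the named time-by-treatment test has much less power than a comparison of patients with any event: about 0.44 vs 0.73, and 0.11 vs 0.39, for a threefold excess per visit. It may not be estimable when attempts are rarer still. Even the any-event test is weak there (0.15 at 0.5% vs 1.5%), so an interval estimate matters more than a p-value.

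These sizes rest on assumed rates, an assumed correlation and complete data. The direction is the same under two event models. For self-injury no size was computed, and the argument rests on the shape of the data. The point concerns one secondary endpoint and does not touch the CAPS-5 analysis. It should be changed before analysis.

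**What to change.** In the Statistical analysis section, exempt suicide attempts and non-suicidal self-injury from the linear mixed model, and state instead:

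- **Attempts:** for all patients in the intent-to-treat sample, compare by arm the proportion with any attempt reported at T2 to T6, as a risk difference with an exact or score 95% confidence interval, and tabulate by visit.
- **Source:** use only assessments made in both arms. The weekly ratings described for DBT-PTSD alone cannot support a fair comparison.
- **Self-injury:** analyse frequency over T2 to T6 with a negative binomial or similar count model.
- **Death by suicide:** count it as an event, not only as missing data.
- **Hospital stays for suicide risk:** tabulate by arm where the reason is recorded.

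The cost is analysis wording only. The items are already collected, and no treatment, hospitalisation or drop-out rule changes. The downside is small: an any-event measure hides the time course, which the table by visit shows.
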